### Outcome measures

2.3.

#### Primary outcome measures

2.3.1.

1.The improvement of the acetabular index2.Severin classification3.The magnitude of limbus inversion4.Avascular necrosis (AVN) of the femoral head was assessed based on the Kalamchi–MacEwen criteria.

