##### Statistical analysis

2.2.1.4.

Statistical analysis was performed using SPSS 27.0 software (IBM, SPSS Inc.).
1.To ensure consistency and reliability between multicenter research samples, it is first necessary to conduct a consistency analysis on the structural data, such as age and sex, of the included cases from each center and the International Hip Dysplasia Institute (IHDI) classification using the Cohen's kappa statistic. Simultaneously, the baseline characteristics (such as structural composition and pathological severity) of the included cohorts within each center must be consistent; imbalances in baseline characteristics were corrected by increasing the sample size.2.The included patients were divided into the non-limbus inversion group (A) and the limbus inversion group based on the presence of limbus inversion at closed reduction. The limbus inversion group was then further divided into the RLI group (B) and the resolved inverted limbus group (C) according to the state at final follow-up. A combination consisting of any two of the groups was organized into cohorts. Fisher's precision probability test was used to compare the difference between the sexes and affected sides, using analysis of variance to compare the different ages between the two groups. Differences in acetabular index was compared using Student's *t*-test. Chi-square test was used to compare IHDI classification, VAS and HHS, and Severin classification at the final follow-up, and analysis of variance was used to compare the MRI T1ρ mapping values and the difference in the initial magnitude of limbus inversion between groups B and C, as well as the difference between the initial magnitude of limbus inversion and that at the final follow-up in group B.3.ROC curve analysis was used to predict the cut-off value of the initial magnitude of limbus inversion in the case of persistent RLI as well as calculate its specificity, sensitivity, and statistical significance.4.Sample size calculation.In this study, ossification of the acetabular cartilage was the main observation; thus, improvement of the acetabular index was the most suitable observation indicator. The sample size calculation was based on the previously published acetabular index at the final follow-up in the group with RLI and the group without RLI after closed reduction (21.41°±3.61° and 18.88 ° ± 4.32° in the two groups, respectively) (15). The significance level *α*, the statistical power of the test, the ratio of the sample sizes in the two groups, and the percentage of patients lost to follow-up were set at 0.05, 0.9, 1:1, and 20%, respectively. The minimum sample size for each group was calculated to be 67 cases (134 cases in total). Therefore, at least 67 cases needed to be enrolled in the observation group and the control group, respectively.

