##### Randomized blocks and interventions

2.2.2.2.

A randomized trial study design was the most appropriate approach to observe the efficacy of surgical intervention, with blinding techniques used during statistical analysis of the data. A double-blind study was not feasible because the surgeon was required to provide detailed information on the surgical regimen. The researchers in each center divided the RLI participants into two study cohorts based on the randomized block design, i.e., the surgery and non-surgery groups. After informed consent was obtained from the guardians of patients in the surgery group, clearance of the inverted limbus *via* arthrotomy was performed.

All surgeries were performed by pediatric hip joint surgeons with senior job titles *via* a bikini incision, and the inverted limbus tissue embedded between the acetabulum and femoral head was excised after arthrotomy without damaging the limbus-cartilage complex. After surgery, casts or braces were applied to immobilize single hips in abduction for 4 weeks and the patients gradually resumed walking after removal of external fixators. No special rehabilitation therapy was administered.

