##### Prospective follow-up observation

2.2.2.3.

Prospective follow-up observation was performed for the two clinical cohorts, and frontal pelvic radiographs were reviewed every 6 months. Since development of the hip joint in children is a long-term process, the included pediatric patients needed to be followed until skeletal maturity. Data pooling was performed once every 2 years to compare the short-term and medium-term outcomes of hip joint morphological development between the two groups. MRI T1ρ mapping was used to quantitatively evaluate quality of the acetabular cartilage before and during postoperative follow-up. The evaluated aspects and parameters were the same as those specified in 2.2.1.

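### Four unranked primary outcomes serve all three parts, although only the acetabular index is sized and limbus inversion is what the randomised surgery removes

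*Protocol article*

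**What the plan says.** Section 2.3.1 of the protocol article lists the primary outcomes once, for the whole programme, without order or assignment to a part: "The improvement of the acetabular index2.Severin classification3.The magnitude of limbus inversion4.Avascular necrosis (AVN) of the femoral head" (the item numbers run into the text).

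Section 2.2.1.4 (part 1, retrospective cohort) takes a different line. It states that "improvement of the acetabular index was the most suitable observation indicator" and sizes on AI alone. Significance level, power, allocation ratio and loss to follow-up "were set at 0.05, 0.9, 1:1, and 20%, respectively", and the result is: "The minimum sample size for each group was calculated to be 67 cases (134 cases in total". The planning values are final AI in two groups, with and without RLI. The same section forms three groups: A (no inversion at closed reduction), B (inversion still present at final follow-up) and C (inversion resolved by then). It adds: "A combination consisting of any two of the groups was organized into cohorts".

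In part 2 (2.2.2, randomised), entry requires limbus inversion above 32% of acetabular roof depth, or the part 1 cut-off (2.2.2.1.1). In the surgery arm "the inverted limbus tissue embedded between the acetabulum and femoral head was excised" (2.2.2.2). Follow-up uses the same parameters as part 1, and "Data pooling was performed once every 2 years to compare the short-term and medium-term outcomes" (2.2.2.3).

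In part 3 (2.2.3.2), inversion above or below the cut-off determines whether a child joins the open-reduction or the closed-reduction cohort. Data are again pooled every 2 years (2.2.3.3).

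**The concern.** Three things do not fit together.

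- **No single primary outcome.** Section 2.2.1.4 chooses AI; 2.3.1 gives three other outcomes the same rank. As written, success could be claimed on any of the four.
- **One of the four cannot measure benefit in parts 2 and 3.** In the randomised part, limbus magnitude is both the entry condition and the tissue removed. A difference between arms would confirm that the operation took place. It would not answer the question in 2.1, whether dysplasia can be reversed after intervention. In part 3 the same variable defines the cohorts.
- **The 90% power belongs to one contrast.** It was calculated for two groups on AI, while the analysis text allows any pair of three groups.

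At stake is a randomised comparison reported as positive on a primary outcome that says nothing about acetabular development, and a power figure read as covering comparisons that it does not cover.

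**Working it through.** **1. Reproduce the sample size (inputs from 2.2.1.4).** AI 21.41 (SD 3.61) versus 18.88 (SD 4.32); α = 0.05; power 0.9; ratio 1:1; 20% loss. Sidedness is not stated. Two-sided is assumed because it reproduces the figure; one-sided gives 54.

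- Difference: 21.41 − 18.88 = 2.53.
- Pooled variance: (3.61² + 4.32²)/2 = (13.032 + 18.662)/2 = 15.847; SD 3.98; standardised difference 2.53/3.981 = 0.636.
- n per group = 2 × (1.960 + 1.282)² × 15.847/2.53² = 2 × 10.51 × 2.476 ≈ 52.0, taken as 53.
- With 20% loss: 53/0.8 = 66.25, so 67 per group and 134 in total. This matches.

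The calculation uses one outcome, two groups and one test. Three groups at the same unadjusted size would need 3 × 67 = 201, so the stated total of 134 fits only one two-group contrast.

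**2. What 53 evaluable per group gives.** Non-centrality: 0.6355 × √(53/2) = 3.272.

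- One contrast at 0.05: Φ(3.272 − 1.960) = 90.5% (90.0% with Welch's t).
- Three pairs at α/3 = 0.0167, as an illustration: Φ(3.272 − 2.394) = 81.0% (79.7% with Welch's t), so about 80%.
- Restoring 90% at α/3: 2 × (2.394 + 1.282)² × 2.476 ≈ 66.9, taken as 67 evaluable; 67/0.8 = 83.75, so 84 enrolled per group, or 252 for three groups.

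**3. Where limbus magnitude is circular.**

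| Part | Role of limbus inversion | As a between-group outcome |
|---|---|---|
| 1, initial magnitude, B vs C | Groups split by final state | Not circular; an empirical question |
| 1, final magnitude, B vs A or B vs C | Final state defines B | Differs by definition |
| 1, final magnitude, A vs C | Neither group has residual inversion | No built-in difference |
| 2 | Entry criterion, then excised in one arm | Shows that surgery was done |
| 3 | Decides the cohort, then excised in one | Differs at baseline by definition; afterwards reflects surgery |

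**4. Cost of leaving the other three unranked.** If AI, Severin class and AVN were each tested at 5% and any one sufficed:

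- Independent: 1 − 0.95³ = 14.3%.
- Simulated with a common correlation of 0.3, 0.5 or 0.7 (assumed): 13.7%, 12.6% and 10.9%.
- AI and Severin only, independent: 1 − 0.95² = 9.75%. This case matters because the part 1 and part 2 analysis paragraphs name no AVN test.

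**The case against.** Several counter-arguments are fair.

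- **A multiplicity rule may sit in the analysis plan or full protocol.** This stands. The 0.05 appears once, as a sample-size input, so testing each outcome at 5% is an assumption, and the absence of an adjustment rule is not the point here. But the four-item list, its conflict with 2.2.1.4 and the two-group sizing are fixed in the article.
- **Limbus magnitude is a proper outcome in part 1.** This stands too. Section 2.1 makes the long-term fate of RLI a main aim. The one between-group limbus test that the article names, initial magnitude in B versus C, is not circular, and the ROC cut-off depends on it. Demoting the variable in part 1 would cut against that aim.
- **Sections 2.2.2.6 and 2.2.3.4 name no limbus test.** True. Its use as a primary outcome in parts 2 and 3 follows from 2.3.1, and for part 2 also from the shared parameters in 2.2.2.3. A listed primary outcome must still be reported.
- **The 67 could mean 67 per group within whichever pair is compared.** Possible, but the stated total of 134 favours a single contrast. The text should settle it.

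A reader might also infer that four primary outcomes are tested over three pairs and again every 2 years, and multiply these into a much larger error rate. The article does not support that. The three pairs exist only in part 1, which is compared at final follow-up; the 2-yearly pooling exists only in parts 2 and 3, which have two groups each. Not every primary outcome is tested in every pair. The number of poolings is not given, nor is it said that a claim may be made at each. Likewise, no figure can be put on the power of B versus A or B versus C separately, because the article gives no expected split between A and C.

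**Conclusion.** The point holds in limited form. Section 2.3.1 gives four outcomes equal primary rank where 2.2.1.4 chooses AI. In the randomised part, limbus magnitude would be positive simply because surgery took place, and in part 3 it is tied to the way the cohorts are formed. The 67 per group is correct and gives 90% power for one AI contrast, RLI versus no RLI, which in the article's groups is B versus A plus C; that mapping is an interpretation of the planning groups.

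The false-positive chance over the three remaining outcomes is about 14%, conditional on 5% per test, independence and all three being tested. It is lower under positive correlation or if fewer are tested. The 80% for three pairs assumes 53 evaluable in each group and an α/3 split, neither of which the article plans.

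This is an inexpensive improvement to the outcome hierarchy. It does not invalidate the design, and it does not make every use of limbus magnitude circular.

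**What to change.** - **Parts 2 and 3:** name AI as the single primary outcome, and say whether it is change or final value (2.3.1 says improvement; the sizing uses final values). Choose one 2-yearly pooling in advance as the primary time point and call the others descriptive. Report limbus magnitude as a process (manipulation) check. Make Severin class and AVN secondary or safety outcomes.
- **Part 1:** keep limbus magnitude as a natural-history outcome (initial magnitude in B versus C, and the ROC cut-off). State that final magnitude in B versus A or B versus C is not counted as a finding, because it defines the groups.
- **Sample size text:** state that 134 gives 90% power only for B versus A plus C on AI, and that the A/B/C pairwise tests are exploratory.

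The cost is wording, with no added recruitment. The downside is that Severin class, AVN and the pairwise results become supportive. If the investigators want all three pairs to be confirmatory at α/3, the price is 84 enrolled per group.

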#### Secondary outcome measures

2.3.2.

1.VAS and HHS2.The T1ρ mapping values

## Discussion

3.

DDH is one of the most common limb deformities in the skeletal system of infants, and its treatment methods usually depend on the pediatric patient's age and the severity of hip joint dislocation and dysplasia. Patients younger than 6 months of age can be treated nonoperatively, whereas pediatric DDH patients aged >6 months or those experiencing failure in treatment with the Pavlik harness require surgical treatment. Closed reduction is an important surgical procedure for achieving concentric reduction of the joint; however, the incidence of post-reduction RAD remains high. The labrum is a fibro-chondral structure attached to the edge of the acetabulum (18). It surrounds the acetabulum in a horseshoe shape, and its ends are connected *via* the transverse ligament, which increases depth of the acetabulum cavity, expands coverage of the femoral head, and enhances joint stability (19). In contrast, the limbus in DDH becomes hyperplastic, hypertrophied, rounded, and inverted relative to the edge of the acetabulum owing to the loss of stimulus for normal growth and the remodeling effect exerted by the femoral head. In morphology, the labrum in DDH is completely different from those observed in normal hips; thus, the pathologic labrum in DDH was referred to as a “limbus” to distinguish it from the morphologically normal labrum. The limbus becomes hypertrophied and surrounded by fibrous tissues, which is a key barrier to concentric reduction (20). With the exacerbation of limbus inversion, stenosis at the entrance of the acetabular cavity becomes increasingly noticeable, which often leads to failure in closed reduction (21, 22). However, RLI is still common even after safe and stable closed reduction is achieved.

At present, the changes and outcomes of the inverted limbus after closed reduction of DDH remain controversial. Severin et al. (23) believed that after achieving stable closed reduction, the inverted limbus would be gradually absorbed and disappear; however, others believed that the inverted limbus was a key factor leading to AVN. Previous studies have been based on indirect observation of x-ray images, and there is a lack of direct evidence regarding the morphological evolution of the inverted limbus. This study used serial MRIs to observe the outcomes of limbus inversion after closed reduction of DDH, which lessened the impact of radiation on pediatric patients and enhanced the safety and reliability of the study. Our previous findings indicated that the magnitude of limbus inversion after closed reduction is closely related to its medium-term morphological outcome (16). However, the previous study had certain limitations since it was based on a small sample and did not follow-up until skeletal maturity. Previous studies have confirmed that a primary limbus inversion leads to primary acetabular dysplasia and early-onset OA (24, 25), but the long-term result of RLI has not been reported in DDH patients who previously underwent closed reduction.

Reaching skeletal maturity of the hip is a long-term process; therefore, the prospective design of this protocol better reflects the relationship between RLI and multiple prognostic outcomes while balancing many known or unknown biases. This research plan is to be led by the corresponding author's institution and carried out by multiple clinical research centers in cooperation with pediatric orthopedic centers in China. Compared to previous case-control studies, this study was designed as a multicenter clinical study with a higher level of evidence. Consistency of the characteristics included in a multicenter sample study is a key issue in clinical research. In the process of sample collection, cohort characteristics within each center are required to achieve homogeneity, which can be solved by increasing the sample size to ensure reliability of the final pooled samples. The follow-up rates in clinical studies are another key issue affecting reliability of the study results. Specialized staff in each center were assigned the task of following included cases, establishing case study databases, and recording various contact methods to guarantee a follow-up rate of over 80%.

The incidence of DDH in China is 1.52% (26).The large basis of the annual newborn population and the large number of patient samples in China are conducive to effectively accumulating study samples within a short period of time, which increases the feasibility of this study protocol. Our research question stems from novel ideas in clinical practice, and this study is the first to suggest that the inverted limbus cannot be absorbed after closed reduction for DDH and is a risk factor of RAD. This study is also the first to discuss the effects of RLI based on clinical practice. By conducting this study, we aim to clarify the effect of RLI on acetabular development after closed reduction of DDH, define the timing and indications for surgical interventions of RLI after closed reduction of DDH, and to inform revision of the criteria for an acceptable closed reduction in DDH treatment so that the incidence of OA caused by RAD after DDH treatment can be reduced in clinical practice.

The exact mechanism by which RLI causes RAD after closed reduction for DDH remains unclear. Wang et al. (27) used latex pads to simulate the inverted limbus embedded between the femoral head and acetabulum of the model hip joint and performed mechanical experiments to confirm that the local contact pressure at the location of the latex pads was significantly increased. Hence, we speculated that persistent imbalance in pressure between the acetabulum and femoral head caused by RLI after closed reduction for DDH is a major factor contributing to RAD. In future studies, we will further perform biomechanical experiments at the cellular level using animal models to provide insights into the mechanism of action of RAD in limbus inversion. It is of great clinical significance to reveal the molecular mechanism by which RLI causes acetabular dysplasia and to obtain robust evidence to guide clinical decisions.

## Ethical considerations

4.

### Research ethics approval

4.1.

The registration of clinical trials was completed prior to this study protocol (registration number: ChiCTR1900020996) and was approved by the Medical Ethics Committee of Shengjing Hospital of China Medical University.

This study will recruit pediatric patients who have undergone closed reduction. Pediatric patients who meet al.l inclusion criteria and do not meet any exclusion criteria will be considered for this study. Prior to enrollment in the study, researchers will explain the objectives and content of the study in detail to the guardians of study participants as well as discuss the surgical risks and benefits of RLI clearance after closed reduction; researchers will ensure that the guardians are fully informed of the study. The guardians of the study participants must provide written informed consent before any research activity may begin. Participation in this study is voluntary and may be withdrawn by the participants' guardians at any time.

### Data collection and management

4.2.

A medical record registration system has been developed according to the study protocol and data analysis plan. To ensure the integrity of critical data, mandatory fields are pre-specified. Instructions for completing medical record registration forms may be accessed within the system, and quality assurance protocols have also been developed. Designated, well-trained qualified investigators will ensure accurate recording of data for all included patients in the medical record registration system. The investigator will review and submit data to specialized data administrator personnel for data entry and management. To ensure the accuracy of the data, double data entry will be performed by two separate investigators; entered data will be verified and validated by software which will prompt for manual error corrections. After the central database administrator confirms that the database is accurate and error-free, the database will be locked. The locked data files are then submitted to an independent statistical team for analysis.

### Confidentiality

4.3.

All study-related information will be securely stored at the study site in areas with access restricted to the research team. All records containing names or other personally identifying information, such as locator forms or informed consent forms, will be stored separately from study records identified by study subject ID numbers. All local databases must be secured using password-protected access systems.
